**Methods:**

A quasi-experimental study will be conducted in rural Bangladesh. Villages will be allocated to the intervention and control areas. Pregnant women (≥16 gestational weeks) will participate together with their infants and will be followed up 1 year after delivery or birth. The intervention will include regular health checkups via the Portable Health Clinic telehealth care system, which is equipped with a series of sensors and an information system that can triage participants’ health levels based on the results of their checkups. Women and infants will receive care 4 times during the antenatal period, thrice during the postnatal period, and twice during the motherhood and childhood periods. The outcomes will be participants’ health checkup coverage, gestational and neonatal complication rates, complementary feeding rates, and health-seeking behaviors. We will use a multilevel logistic regression and a generalized estimating equation to evaluate the intervention’s effectiveness.

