### Sample Size

All eligible women and infants at the study sites will be included in our study. Approximately 1000 mother-infant dyads have been deemed eligible for this study among all clusters (500 dyads in each cluster). However, the minimum sample size for recruitment was calculated as 925 dyads for all clusters; 771 dyads in a cluster are required for analyses based on our pilot study, in which the percentage of antenatal care increased by ≥4 times (from 29% to 42%). A 2-tailed test will be conducted (power=0.95; α error=.05). A loss to follow-up rate of 20% was estimated.

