### Statistical Analyses

First, we will conduct descriptive analyses of and comparison tests between the intervention and control clusters to assess their similarities. Second, to evaluate the effectiveness of the intervention and compare the clusters, we will perform a multilevel logistic regression model of end line surveys, adjusting for the effects of clustering. Finally, sensitivity analyses will be conducted to assess the robustness of the model. The statistical significance will be set at a *P* value of <.05. All data analyses will be performed by using IBM SPSS (IBM Corporation).

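### The stated power of 0.95 treats women as independent, but six whole villages are allocated, three per area; with plausible between-village variation the power is well below 0.95

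*Protocol article*

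**What the plan says.** The Sample Size section bases the calculation on a pilot study "in which the percentage of antenatal care increased by ≥4 times (from 29% to 42"%), meaning that uptake of four or more antenatal visits rose from 29% to 42%. It then states "A 2-tailed test will be conducted (power=0.95; α error=.05"). It gives these counts:

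- available: "Approximately 1000 mother-infant dyads have been deemed eligible for this study among all clusters (500 dyads in each cluster")
- to recruit: "the minimum sample size for recruitment was calculated as 925 dyads for all clusters"
- to analyse: "771 dyads in a cluster are required for analyses based on our pilot study"
- attrition: "A loss to follow-up rate of 20% was estimated"

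On the design, the abstract says "Villages will be allocated to the intervention and control areas". Study Design and Sites names three intervention and three control villages, purposively chosen within one Union. Statistical Analyses evaluates effectiveness with a multilevel logistic regression of the end line survey, "adjusting for the effects of clustering". The article gives no ICC or design effect anywhere, and the sample-size text does not use the number of villages.

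The article uses the word cluster for a whole study area. Below, area means the three villages of one arm, and village means the unit that was allocated.

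**The concern.** The analysis allows for similarity of women within a village, but the power statement behind it does not. When whole villages are allocated, the variance of the difference between areas has a between-village part. That part shrinks with the number of villages, not with the number of women. With about 130 women in each of three villages per area, a small ICC is enough to raise the variance noticeably.

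A power of 0.95 tells the reader that a 13-point gain would be missed only one time in twenty. If the true figure is nearer one in two, a null result could be taken as good evidence against a gain that the study could easily have missed.

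**Working it through.** **Inputs from the article.** p₁ = 0.29, p₂ = 0.42, two-sided α = 0.05, power 0.95, 771 to analyse, 925 to recruit, about 500 eligible per area, 20% loss (all Sample Size); three villages per area (Study Design and Sites).

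**Assumption.** The ICC. I used 0.005 to 0.05. Around the mean uptake of 35.5%, an ICC of 0.01 is a between-village standard deviation of √(0.01 × 0.355 × 0.645) = 0.048, about 5 percentage points.

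**Reading of 771.** The text attaches 771 to one cluster. That conflicts with 925 for all clusters and with 500 available in each. Since 771 × 1.2 = 925, I read 771 as the total, or 385.5 per area. The literal reading is tested at the end.

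**1. Reproducing the stated figure with independent women.**
- The standard two-proportion formula at power 0.95 gives 350 per area, 700 in total, or 730 with continuity correction.
- With 385.5 per area the power is 0.966. The stated 0.95 therefore reproduces approximately as an individual-level figure.
- The exact 771 was not reproduced from the printed percentages. Rounding in them could account for it: 29% vs 41.5% gives 754 without correction and 786 with it.
- If the excess over 700 were a clustering allowance, the design effect would be 771/700 = 1.10. That implies an ICC of 0.10/(128.5 − 1) ≈ 0.0008.

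**2. Power with villages as the unit.**
- Analysed per area: 500 × 0.8 = 400, so m = 400/3 = 133.3 women per village.
- Design effect: DE = 1 + (m − 1) × ICC.
- Variance sum: 0.29 × 0.71 + 0.42 × 0.58 = 0.2059 + 0.2436 = 0.4495.
- Standard error: SE = √(0.4495/400 × DE).
- Normal-test power: Φ(0.13/SE − 1.96).
- Power on 4 degrees of freedom (six villages less two areas): noncentral t with noncentrality 0.13/SE and critical value 2.776.

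Example at ICC 0.01: DE = 1 + 132.3 × 0.01 = 2.32; SE = √(0.4495/400 × 2.32) = 0.0511; 0.13/0.0511 = 2.54; Φ(2.54 − 1.96) = 0.72.

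| ICC | DE | Power, normal | Power, t on 4 df |
|---|---|---|---|
| 0 | 1.00 | 97% | 82% |
| 0.005 | 1.66 | 85% | 62% |
| 0.01 | 2.32 | 72% | 49% |
| 0.02 | 3.65 | 53% | 34% |
| 0.05 | 7.62 | 29% | 19% |

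Normal-test power reaches 0.95 only for ICC ≤ 0.0012 (≤ 0.0009 with 385.5 per area).

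**3. Difference from 29% detectable with 80% power, 400 per area.**

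| ICC | Normal | t on 4 df |
|---|---|---|
| 0.005 | 12 points | 16 points |
| 0.01 | 14 points | 19 points |
| 0.02 | 18 points | 24 points |

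**4. More favourable cases.**
- All 500 per area with no loss: 76% (normal) and 52% (t) at ICC 0.01; 0.95 needs ICC ≤ 0.0027.
- Literal 771 per area, which exceeds the 500 available: 81% and 58% at ICC 0.01; 0.95 needs ICC ≤ 0.0048.
- Unlimited women in the same villages, SE = √(0.4495/3 × ICC): 92% and 71% at ICC 0.01; 66% and 44% at 0.02; 32% and 21% at 0.05. At an ICC of 0.01 or more, no number of women in these six villages gives 0.95.

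**The case against.** **The ICC is unknown.** All six villages lie in one Union, and the areas were matched on population size, location and access to a health facility, so between-village variation may be small. It is true that the size of the shortfall is conditional on the ICC. That 0.95 requires an ICC close to zero does not depend on where in the range the true value lies.

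**The 4-df figures assume a test the protocol does not name.** The article plans a multilevel logistic model, and its abstract adds a generalized estimating equation. How to handle six villages in the inference may be settled in a document not shown. This is fair, and it is why both sets of figures are given. The normal-test figures are the favourable ones, and they already fall below 0.95 at every ICC from 0.005 up. At ICC 0.005 that test still detects 12 points with 80% power, so the study is not without value.

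**Loss of 20% may not apply to control women**, who have no checkup schedule. With all 500 per area the ICC limit rises to 0.0027, which does not restore 0.95.

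**Nothing in the conduct changes.** All eligible women are taken and the model adjusts for clustering, so its interval should carry the extra uncertainty. That limits the harm to the power claim, but adjusting at analysis does not supply the power.

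**A baseline ICC from six villages is imprecise.** This stands. At an estimated 0.01 with 133 women per village, the variance ratio is about 1 + 133 × 0.01/0.99 = 2.3. Chi-square limits on 5 degrees of freedom then give an approximate 95% interval for the ICC of 0 to 0.09. A range is needed, not a single estimate.

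**Conclusion.** The concern holds. The stated 0.95 matches a calculation for independent women and cannot be supported for three villages per area unless the between-village ICC is near zero: at most 0.0012 with 400 analysed per area and a normal test. For ICCs of 0.005 to 0.05, power for 29% vs 42% is 85% down to 29% by the normal test, and 62% down to 19% on 4 degrees of freedom. The ICC range is my assumption, since the article gives none. The figures also assume equal village sizes, 20% loss in both areas and 771 read as a total. Relaxing the last two does not restore 0.95 anywhere in that range.

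**What to change.** Withdraw the power of 0.95 from the Sample Size section. In its place, give power or the detectable difference for six villages, with the expected number of women per village and a stated ICC range, for example 0.005 to 0.05. Say whether the figures rest on a normal test or on a small number of degrees of freedom. State that 771 is the total, if that is what was meant.

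Estimate the ICC from the baseline survey of the same six villages before the end line analysis, and report it with its uncertainty alongside the assumed range. Present the end line result as an estimate with a cluster-adjusted confidence interval, so that a null finding is read from the interval and not from the planned power.

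The cost is a change of wording and a short calculation. Recruitment, outcomes and data collection are unaffected. The stated power becomes less favourable. The article places analysis after the end of data collection, so on its own timeline the correction can be made before end line data are analysed.

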### Statistical Analyses

First, we will conduct descriptive analyses of and comparison tests between the intervention and control clusters to assess their similarities. Second, to evaluate the effectiveness of the intervention and compare the clusters, we will perform a multilevel logistic regression model of end line surveys, adjusting for the effects of clustering. Finally, sensitivity analyses will be conducted to assess the robustness of the model. The statistical significance will be set at a *P* value of <.05. All data analyses will be performed by using IBM SPSS (IBM Corporation).

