## Methods

### Study Design and Sites

Our study is quasi-experimental, and it will be conducted in 6 villages within the Chhaygaon Union of Bhedarganj Upazila (subdistrict), Shariatpur District, Bangladesh (Figure 1; trial registration number: ISRCTN44966621). Located approximately 80 km from Dhaka, these villages are in the suburb of the capital. Among the nine villages in the Chhaygaon Union, the East Chhaygaon, Middle Chhaygaon, and Lakarta villages were purposively set as the intervention cluster, and the Gangshar, Nazimpur, and Aterpara villages were set as the control cluster. The villages were allocated to the intervention and control areas such that the population sizes (intervention area: N=6378; control area: N=6178), geographic locations of the villages, and access to health facilities (each area has a health facility) were similar between the two areas. In the intervention arm, we conducted a pilot study in which we used the PHC system between June 2019 and May 2020 to follow women and infants from 16 gestational weeks to only 6 weeks post partum, with a shorter postpartum follow-up period than the one described herein.

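### Comparison tests at P<.05 cannot establish that two purposively chosen areas are similar; ignoring villages, they miss an imbalance of half the planned effect about 40% to 51% of the time

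*Protocol article*

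**What the plan says.** Under Statistical Analyses, the protocol article's first step is a descriptive analysis together with "comparison tests between the intervention and control clusters to assess their similarities". The same section adds, for the study as a whole, "The statistical significance will be set at a *P* value of <.05". It gives no margin within which the areas would count as similar, and it does not say what follows from a significant or a non-significant result.

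The second step is a multilevel logistic regression on the end line surveys. The only adjustment named for it is clustering. Sensitivity analyses follow, without detail.

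Study Design and Sites says that three villages were purposively assigned to each area, so that population size, location and "access to health facilities (each area has a health facility) were similar between the two areas". Baseline and End Line Survey says that the questionnaires collect sociodemographic and economic status and the health services received.

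For scale, Sample Size says: "Approximately 1000 mother-infant dyads have been deemed eligible for this study among all clusters (500 dyads in each cluster". Its planning effect is a rise from 29% to 42%, read here as the share of women with at least four antenatal visits.

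**The concern.** The tool does not match its stated purpose. A difference test asks whether the data contradict equality. A non-significant result may mean that the areas are alike, or that the sample was too small to show that they differ. Only the estimated difference and its interval separate the two.

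This matters more here than in a randomised trial. The villages were chosen, so true differences should be expected, and the useful question is how large they are. Matching is described for population, location and facility access. The Introduction names other influences on care use (family wealth, previous childbirth, women's autonomy), and the article claims no matching on those. The effectiveness model names no covariate beside clustering. Belief that the areas are comparable therefore carries much of the causal reading of the end line difference. If a table of non-significant P values is taken as support for that belief, a moderate imbalance could remain inside the reported intervention effect.

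**Working it through.** **Inputs**
- Two-sided α = 0.05 (Sample Size: "A 2-tailed test will be conducted (power=0.95; α error=.05"; the same level under Statistical Analyses).
- Reference rate 29% and planned effect 42% − 29% = 13 points (Sample Size).
- Women per area: 500 (Sample Size) as the upper value; 771/2 = 385.5, taken as 386, as the lower value.
- Assumption: the similarity check uses 386 to 500 women per area. The article does not say how many women the baseline survey will reach.

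**The plan's own figure.** Sample Size states: "the minimum sample size for recruitment was calculated as 925 dyads for all clusters; 771 dyads in a cluster are required for analyses". The 771 can be smaller than the 925 for all clusters only if it is the two-area total. The standard two-proportion formula, with p̄ = 0.355, is

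n = [1.96·√(2·p̄(1−p̄)) + 1.645·√(0.29·0.71 + 0.42·0.58)]² / 0.13² ≈ 350 per area, or 700 in total.

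This does not reproduce 771. Rounding of the pilot rates could explain the gap, since 29.4% against 41.8% gives 770. The recruitment figure follows from 771 × 1.2 = 925. The point below does not depend on this; 771 serves only as the lower sample size.

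**Power of an individual-level comparison test, villages ignored.** For a true imbalance d from 29%:

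power = Φ[(d − 1.96·SE₀)/SE₁], where SE₀ = √(2·p̄(1−p̄)/n), SE₁ = √([p₁(1−p₁) + p₂(1−p₂)]/n), p₁ = 0.29 and p₂ = 0.29 + d.

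Example with d = 0.065 and n = 500: SE₀ = 0.02956 and SE₁ = 0.02949. Then (0.065 − 0.05794)/0.02949 = 0.239, so power is 0.595 and the miss rate 0.405.

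| True imbalance | Missed, 500 per area | Missed, 386 per area |
|---|---|---|
| 5 points | 60.2% | 67.9% |
| 6.5 points (half the effect) | 40.5% | 51.1% |
| 10 points | 8.3% | 16.4% |
| 13 points (the whole effect) | 0.9% | 3.4% |

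The test misses more often than it detects only below about 5.8 points (500 per area) or 6.6 points (386 per area).

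**What an interval would show.** With equal true rates of 29%, the 95% half-width is 1.96·√(2·0.29·0.71/n). That is ±5.6 points at 500 and ±6.4 points at 386, again ignoring villages. A non-significant result near zero is thus compatible with an imbalance of nearly half the planned effect. The interval says so and the P value does not.

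**Villages.** With m women per village and intracluster correlation ICC, the variance grows by 1 + (m − 1)·ICC, and six villages in two areas leave 4 degrees of freedom for an area contrast. Both lower power, so a test that respected villages would miss more than the table shows. The article gives no ICC, so no figure is attached.

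**The case against.** **No acceptance rule is written.** A reader might infer that P>.05 will be taken as proof of comparability. The article does not say so. Its significance level is general, nothing is stated to hang on the result, and descriptive analyses, which can show the size of differences, are planned beside the tests. This stands. What remains is that a difference test is named as a means of assessing similarity, a purpose it cannot serve.

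**Large imbalances would be seen.** A reader might also infer that the tests usually miss differences big enough to imitate the whole intervention effect. For individual-level tests at the document's own numbers that is wrong: a 13-point imbalance is detected 97% to 99% of the time. The loss is in moderate imbalances.

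**Village-level failure rates are not the plan's.** One could compute very high miss rates for a t-test of three villages against three. The article names no such test and gives no ICC, so only the direction can be claimed.

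**End line false positives belong elsewhere.** An unadjusted individual-level end line test would be significant about 40% of the time under a persistent 5-point difference and no intervention effect. That is its ordinary power for 5 points; the baseline test plays no part in it, and it is not a property of the planned multilevel model.

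**A full protocol or analysis plan may say more.** Covariate lists and table layouts are often left to those documents, and their absence from an article is no fault. The point rests on the method that the article does state.

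**Conclusion.** The point holds in a limited form. Difference tests at P<.05 cannot establish that the two areas are similar. Ignoring villages, they would miss a 5-point imbalance 60% to 68% of the time and one of half the planned effect about 40% to 51% of the time. They would rarely miss an imbalance as large as the whole effect. The figures assume 386 to 500 women per area and a 29% rate; fewer baseline respondents, or allowance for villages, would raise the miss rates. The documents do not support saying that the investigators have adopted non-significance as a rule for comparability, only that the stated method leaves room for that reading.

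**What to change.** In Statistical Analyses, replace the comparison tests by wording such as: characteristics and survey outcomes will be summarised by area and by village, with raw and standardised between-area differences and 95% confidence intervals; comparability will not be inferred from P>.05. Add that the end line multilevel model will adjust for a prespecified set of sociodemographic and economic covariates from the surveys, kept whatever imbalance is observed.

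No fixed cut-off for the standardised difference is needed. With 500 women per area, P<.05 already corresponds to about 1.96·√(2/500) = 0.124, so a cut-off of 0.1 would flag chance village variation more often than the tests it replaced.

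The cost is a change of wording and a different table. The surveys already collect the data, and Results says that analysis starts only after data collection ends, so no extra women or procedures are required. The small downside is that the report must show whatever imbalances exist and cannot claim similarity from non-significance.

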### Data Collection Methods and Evaluation

We will assess the impact of the intervention by comparing the clusters, using baseline and end line questionnaire survey data.

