#### Baseline and End Line Survey

We will conduct the questionnaire survey at the baseline and end line periods for all eligible women in the intervention cluster and control cluster. The questionnaire items assess sociodemographic and economic status, the health services received and the times they were received, symptoms during pregnancy, and postpartum or neonatal complications. The PHC-MNCH researchers developed the survey in English, and the research assistants translated it into Bengali. A Bengali- and Japanese-speaking researcher then checked the accuracy of the translation.

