### Study Outcomes and Measurements

The following outcomes will be compared based on the baseline and end line surveys: the frequency of antenatal and postnatal care visits by health care providers conducted through health checkups with the PHC or at health facilities; the detection rate of gestational complication symptoms (suspected gestational diabetes, pregnancy-induced hypertension, anemia, preterm birth, and postterm birth); the detection rate for neonates and infants with suspected jaundice, anemia, and growth delay; the percentage of infants who started complementary feeding at 6 months after birth; and the percentage of participants who sought health care or exhibited health-seeking behaviors or self-care behaviors upon experiencing health problems.

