## Discussion

In our study, the intervention arm participants are expected to have better health statuses than those of the control arm, as they will receive care through the PHC-MNCH. Our community-based intervention study is extremely important for realizing the continuum of care in MNCH through a telehealth care system and evaluating the improvement of mothers’, newborns’, and children’s health status. Previous studies that investigated the effectiveness of the continuum of care in MNCH mostly focused on the perinatal period [20,21]. Through our trial, we will attempt to show whether the continuum of care, which extends from the antenatal period to the motherhood and childhood periods, is effective in improving the health of mothers and infants. The study will further accumulate evidence on the effectiveness of the continuum of care.

Our proposed study also has a limitation. The intervention sites include some of the areas where we conducted the pilot study. Therefore, some residents of the intervention sites may have a better understanding of the continuum of care than those in the control group. However, since the participants in the pilot study are not included in the proposed study, the effectiveness of the intervention will be evaluated based on its status prior to the pilot study. As such, we believe that this limitation can be controlled.

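### The effectiveness model is fixed to end line data, although the rest of the protocol promises a baseline and end line evaluation, so any remaining pre-existing gap between the purposively chosen areas enters the effect estimate in full

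*Protocol article*

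**What the plan says.** The Statistical Analyses section has three steps. The first is descriptive comparison and tests of similarity between the areas. The second is the effectiveness analysis: "we will perform a multilevel logistic regression model of end line surveys, adjusting for the effects of clustering". The third is sensitivity analyses, whose content is not given.

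Three other sections describe the evaluation differently:

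- Data Collection Methods and Evaluation: "We will assess the impact of the intervention by comparing the clusters, using baseline and end line questionnaire survey data".
- Study Outcomes and Measurements: "The following outcomes will be compared based on the baseline and end line surveys".
- Discussion, answering the concern that the pilot ran in the intervention area: "the effectiveness of the intervention will be evaluated based on its status prior to the pilot study".

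The abstract names a generalized estimating equation beside the multilevel logistic regression. The Statistical Analyses section does not mention it.

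On design, three "villages were purposively set as the intervention cluster" and three others as control. Population size and geographic location were balanced, and "access to health facilities (each area has a health facility) were similar between the two areas". The pilot ran in the intervention arm from June 2019 to May 2020. The surveys cover both areas: "We will conduct the questionnaire survey at the baseline and end line periods for all eligible women in the intervention cluster and control cluster". On content: "The questionnaire items assess sociodemographic and economic status", along with services received and complications.

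**The concern.** In a non-randomised comparison of two areas, the baseline survey is the main means of separating the intervention from differences that were already there. The stated model leaves it out. The Introduction lists family wealth, previous childbirth, women's autonomy and distance to facilities as determinants of care use. The allocation addressed distance through location and facility access. Wealth, childbirth history, autonomy and prior care uptake are not among the stated matching factors.

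A random effect for village does not help with this. Treatment is constant within a village, so the random effect widens the standard error and leaves a systematic area difference inside the treatment coefficient. The bias can go either way: a better-served intervention area would produce a spurious effect, and a worse-served one would hide a real effect.

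The Discussion concludes that the pilot limitation can be controlled because evaluation is made against pre-pilot status. Under the stated model no such evaluation takes place.

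**Working it through.** **Inputs from the protocol (Sample Size):** planning rates 29% and 42%; about 500 dyads per area; 20% loss, so 500 × 0.80 = 400 women per area at end line; two-sided α 0.05; power 95%. Three villages per area (Study Design and Sites).

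**Assumptions, not in the protocol:** pre-existing gaps of 5 and 8 points that persist to end line; village ICC 0.02; 500 baseline women per area. These show a range and are not a prediction.

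**The plan's own calculation.** The standard two-proportion formula for 29% against 42% at 95% power gives (1.960·√(2·0.355·0.645) + 1.645·√(0.29·0.71 + 0.42·0.58))² / 0.13² ≈ 350 per area, 700 in all. The stated 771 is not reproduced. That is a separate matter, and 771 is not used below.

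**1. Size of the bias.** With no true effect, the expected end-line difference equals the gap g. A 5-point gap is 5/13 = 38% of the planned 13-point effect, and an 8-point gap is 62%. As odds ratios from a 29% base: 34% gives (0.34/0.66)/(0.29/0.71) = 1.26, 37% gives 1.44, and the planned 42% gives 1.77.

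**2. Chance of P<.05 with no true effect** = Φ(g/SE − 1.96).

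- *Clustering ignored:* SE² = [0.29·0.71 + (0.29+g)(0.71−g)]/400.
  - g = 0.05: SE = 0.0328, Φ(1.524 − 1.96) = 33%.
  - g = 0.08: SE = 0.0331, Φ(2.415 − 1.96) = 68%.
- *Village ICC 0.02:* τ² = 0.02·0.355·0.645 = 0.00458; add 2τ²/3 = 0.00305 to SE².
  - g = 0.05: SE = 0.0643, Φ(0.778 − 1.96) = 12%.
  - g = 0.08: SE = 0.0644, Φ(1.242 − 1.96) = 24%.
  - A noncentral t on 4 df (six villages less two areas) in place of the normal gives about 9% and 16%.

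Allowing for clustering lowers the rejection rate, but the shift in the estimate stays at 5 or 8 points.

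**3. What using the baseline does.** The difference in differences has expectation zero in these cases if the areas share a common trend.

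**4. What it costs.** True effect 29% to 42% in the intervention area, 29% in the other three cells.

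- *Clustering ignored, end line only:* SE² = (0.2059 + 0.2436)/400 = 0.001124, SE = 0.0335, power Φ(0.13/0.0335 − 1.96) = 97%.
- *Clustering ignored, differenced:* add 2·0.2059/500 = 0.000824, giving SE² = 0.001947, SE = 0.0441, power 84%. With 400 baseline women per area it is 80%.
- *ICC 0.02:* the village term is 2τ²/3 for end line only and 4τ²(1−r)/3 when differenced, where r is the correlation of village levels over time.

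| Analysis | SE (points) | Power |
|---|---|---|
| End line only | 6.5 | 52% |
| Differenced, r = 0.8 | 5.6 | 64% |
| Differenced, r = 0.5 | 7.1 | 45% |

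The two standard errors are equal at r ≈ 0.63. Below that, differencing costs precision; above it, differencing gains precision.

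**5. Pilot participants.** The Discussion says they are not included, but the Study Population and Selection Criteria section lists no such criterion. The birth windows do most of the work: baseline births end in May 2019, before the pilot, and end line births start in November 2020, roughly when a woman at 16 weeks in late May 2020 would deliver. A pilot woman's later pregnancy is not covered.

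**The case against.** The strongest defence is that a journal article condenses the plan. The section does not exclude covariates, sociodemographic data are collected, sensitivity analyses are announced, and the abstract's generalized estimating equation might have been meant for both surveys. The areas were also deliberately balanced on three features.

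Much of this stands, and it limits the point. A reader might infer that the analysis adjusts for no confounders, or that the baseline serves only the similarity check. The text supports neither: it is silent on covariates, which an analysis plan not shown may supply, and it does not say which survey the similarity tests use. Nor does every prior difference pass through, given the matching. The 33% and 68% should not be read as error rates of the planned model either, because they ignore clustering and the planned model is multilevel. Nor does the text imply that the pilot pregnancies themselves enter the surveys, since the birth windows largely prevent it.

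The contradiction is untouched by the defence. The section names the dataset for the effectiveness model, and it is not the one promised in three other places. A method mentioned once in the abstract without data, terms or estimand cannot reconcile them. It is also fair that differencing has a price and that an area-by-period model is one option among several. That argues for stating the price and does not support leaving the baseline out.

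**Conclusion.** The point holds as a contradiction on the main analysis with a real consequence for validity. As written, the effectiveness estimate carries any persisting, unmatched area difference in full, and the Discussion's statement that the pilot limitation is controlled does not follow from the stated model. How large the bias would be is unknown, because the protocol gives no baseline rates by area. An assumed 5- to 8-point gap would amount to 38% to 62% of the planned effect. With an ICC of 0.02 and a normal reference it would be declared significant in about 12% to 24% of studies with no true effect, and in 33% to 68% if clustering were ignored.

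The missing exclusion of pilot women's later pregnancies is secondary.

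**What to change.** Reconcile the abstract, Data Collection Methods and Evaluation, Study Outcomes and Measurements, Statistical Analyses and the Discussion on one main analysis. Suggested content:

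- Fit a logistic model to the pooled baseline and end line records with area, period and area-by-period terms, the last being the effect.
- Account for village clustering and include the same sociodemographic covariates from both surveys.
- Keep the end-line-only model as a sensitivity analysis.
- Either define the generalized estimating equation (data, terms, purpose) or remove it.
- Align the selection criteria with the Discussion on pilot participants, and apply any exclusion in the same way in both areas.

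No new data are needed: both surveys already cover both areas, and analysis starts only after data collection ends. The costs should be written into the plan:

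- Parallel trends must be assumed.
- The pilot fell between the two survey windows in the intervention area, so the area-by-period estimate may include its carry-over.
- Village terms rest on six villages.
- Power falls from about 97% to about 84% ignoring clustering, below the stated 95%. With clustering it depends on how stable village levels are over time. The power statement should be recalculated for the model actually adopted.
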